#### 8.1.3 Other study parameters

N.a.

### 8.2 Randomization, blinding and treatment allocation

N.a.

### 8.3 Study procedures

The study consists of three phases: the pre-intervention phase, the implementation phase and the post-intervention phase (figure 1).

[figure not shown]

Figure 1: Phases during the study

### 8.3.1 Pre-intervention phase

During a 9-month period usual care is provided to patients. This means that antithrombotic therapy, related patient instructions and handover after discharge are carried out by the physicians responsible for the patient. Patients that are or will be treated with antithrombotics in the Erasmus MC and in the Reinier de Graaf hospital will be included with the help of a clinical rule. The criteria on which the clinical rule screens are the use of antithrombotic drugs which are listed in table 1 and the use of antidotes which are listed in table 2.

Table 1: Antithrombotic agents

| Group of antithrombotic agents (ATC code) | Antithrombotic agents (ATC code) |
|-------------------------------------------|----------------------------------|
| Vitamin K antagonists (B01AA)             | Phenprocoumon (B01AA04)          |
|                                           | Acenoucoumarol (B01AA07)         |
| Heparin group (B01AB)                     | Heparin (B01AB01)                |
|                                           | Antithrombin III (B01AB02)       |
|                                           | Dalteparin (B01AB04)             |
|                                           | Enoxaparin (B01AB05)             |
|                                           | Nadroparin (B01AB06)             |
|                                           | Danaparoid (B01AB09)             |
|                                           | Tinzaparin (B01AB10)             |
| Direct thrombin inhibitors (B01AE)        | Bivaluridin (B01AE06)            |
|                                           | Dabigatran etexilate (B01AE07)   |
| Direct factor Xa inhibitors (B01AF)       | Rivaroxaban (B01AF01)            |
|                                           | Apixaban (B01AF02)               |
| Other antithrombotic agents (B01AX)       | Fondaparinux (B01AX05)           |

Table 2: Antidotes

| Group of antihemorrhagics (ATC code) | Antihemorrhagics (ATC code)                                   |
|--------------------------------------|---------------------------------------------------------------|
| Amino acids (B02AA)                  | Tranexamic acid (B02AA02)                                     |
| Vitamin K (B02BA)                    | Phytomenadione (B02BA01)                                      |
| Fibrinogen (B02BB)                   | Fibrinogen, human (B02BB01)                                   |
| Blood coagulation factors (B02BD)    | Coagulation factor IX, II, VII and X in combination (B02BD01) |
|                                      | Eptacog alfa (activated) (B02BD08)                            |
| Antidotes (V03AB)                    | Protamine (V03AB14)                                           |

New antithrombotic agents and antihemorrhagics entering the market, are also included in the study when they are introduced in the hospital.

During the hospitalization for each included patient data are collected in a case report form (CRF). Detailed information on the data can be found in table 3.

Table 3: Content of case report (CRF)

| Part           | Data content                                                                                                                                                                                                                                          |
|----------------|-------------------------------------------------------------------------------------------------------------------------------------------------------------------------------------------------------------------------------------------------------|
| Patient data   | Patient ID                                                                                                                                                                                                                                            |
|                | Date of birth*                                                                                                                                                                                                                                        |
|                | Gender*                                                                                                                                                                                                                                               |
|                | Weight on the first day of hospitalization*                                                                                                                                                                                                           |
|                | Length*                                                                                                                                                                                                                                               |
|                | Community pharmacist**\$                                                                                                                                                                                                                              |
|                | Reason for hospitalization*                                                                                                                                                                                                                           |
|                | Reason for exclusion                                                                                                                                                                                                                                  |
|                | (Co)morbidity*                                                                                                                                                                                                                                        |
|                | Day of hospitalization*                                                                                                                                                                                                                               |
|                | Any surgery (coded with Verrichtingen code  ) or diagnosis during hospitalization*                                                                                                                                                       |
| Study outcomes | Bleeding (major bleeding and mild to moderate clinical relevant non-major bleeding) or thrombotic event during hospitalization*                                                                                                                       |
|                | Bleeding (major bleeding and mild to moderate clinical relevant non-major bleeding) or thrombotic event within 3 months after hospitalization^                                                                                                        |
|                | Severity of bleeding complication*                                                                                                                                                                                                                    |
|                | Hospital discharge date*                                                                                                                                                                                                                              |
|                | Date of each readmission in the following 3 months after the first hospitalization*^                                                                                                                                                                  |
|                | The reason for readmission^                                                                                                                                                                                                                           |
|                | Quality of life  (3 months after discharge):\$
- Age 0-3: no EQ-5D-Y available
- Age 4-7: EQ-5D-Y proxy version 1
- Age 8-11: EQ-5D-Y or EQ-5D-Y proxy version 1
- Age 12-15: EQ-5D-Y or EQ5D
- Age 16 and older: EQ5D |
|                | Adherence by the patient to the therapy; MARS5  (3 months after discharge)\$                                                                                                                                                          |
|                | Patient satisfaction about the quality of care of the antithrombotic therapy; VAS satisfaction scale  (3 months after discharge)\$                                                                                                       |
|                | Adherence to the hospital protocol                                                                                                                                                                                                                    |

|                 |                                                                                                                                                                                                                                                                                                                                                                                                                                                                                                                                                                                                                                            |
|-----------------|--------------------------------------------------------------------------------------------------------------------------------------------------------------------------------------------------------------------------------------------------------------------------------------------------------------------------------------------------------------------------------------------------------------------------------------------------------------------------------------------------------------------------------------------------------------------------------------------------------------------------------------------|
|                 | Percent time in therapeutic range (TTR) of vitamin K antagonists during hospitalization and as an outpatient during 3 months follow-up*                                                                                                                                                                                                                                                                                                                                                                                                                                                                                                    |
|                 | All-cause mortality**                                                                                                                                                                                                                                                                                                                                                                                                                                                                                                                                                                                                                      |
| Clinical data   | 
Laboratory values and the date of determination**
 
 
- International Normalized Ratio (INR)
 
- Activated Partial Thromboplastin Time (APTT)
 
- Prothrombin time (PT)
 
- Diluted Thrombin Time (dTT)
 
- Hemoglobin (Hb)
 
- Antifactor Xa (Anti-Xa)
 
- Creatinine
 
- Hematocrit (HT)
 
- Erythrocytes
 
- Thrombocytes
 
- Estimated Glomerular Filtration Rate (eGFR)
 
- Weight
 
 
(Available clinical data is collected from 3 months before inclusion till 3 months after hospitalization)
 |
| Medication data | Medication use during hospitalization (coded with ATC-code  )*                                                                                                                                                                                                                                                                                                                                                                                                                                                                                                                                                                |
|                 | Use of antidotes: vitamin K, protamine sulfate, prothrombin complex concentrate, fibrinogen, tranexamic acid and recombinant factor VIIa (coded with ATC code  )*                                                                                                                                                                                                                                                                                                                                                                                                                                                             |
|                 | Use of blood products: blood transfusion and other blood products*                                                                                                                                                                                                                                                                                                                                                                                                                                                                                                                                                                         |
|                 | Overview of medication use three months before hospitalization (coded with ATC-code  )+                                                                                                                                                                                                                                                                                                                                                                                                                                                                                                                                       |
|                 | Overview of medication use three months after hospitalization (coded with ATC-code  )+                                                                                                                                                                                                                                                                                                                                                                                                                                                                                                                                        |

\*Obtained from medical record of the hospital information system

+Obtained from the community pharmacist and the Thrombosis Service

\$Obtained from the patient using questionnaire

^Obtained by sending a small questionnaire asking for visits to the general practitioner or hospital because of a bleeding or thrombotic event within 3 months after hospitalization.

***The primary outcome of the study is the proportion of patients with a composite endpoint consisting of  $\geq 1$  bleeding (major bleeding and mild to moderate clinical relevant non-major bleeding) or  $\geq 1$  thrombotic events during and 3 months after hospitalization.***

Patients treated with antithrombotics and/or antidotes in the Erasmus MC and in the Reinier de Graaf hospital will be included with the help of a clinical rule (table 1 and 2). The data from the medical record of the hospital information system is used to determine whether there is a bleeding (major bleeding and mild to moderate clinical relevant non-major bleeding) or thrombotic event in patients who are enrolled in the study.

After hospitalization data from community pharmacist, general practitioner and the Thrombosis Services are used. At discharge the patient will be asked to fill in a consent form. By signing the consent form, the patient gives permission to retrieve patient data from the community pharmacist, general practitioner and the Thrombosis Services.

Definition of terms:

The ISTH definitions of bleeding in patients are as follows:

- Major Bleeding in non-Surgical Patients
  - 1. Fatal bleeding, and/or
  - 2. Symptomatic bleeding in a critical area or organ, such as intracranial, intraspinal, intraocular, retroperitoneal, intra-articular or pericardial, or intramuscular with compartment syndrome, and/or
  - 3. Bleeding causing a fall in hemoglobin level of  $20 \text{ g L}^{-1}$  ( $1.24 \text{ mmol L}^{-1}$ ) or more, or leading to transfusion of two or more units of whole blood or red cells.
- Major bleeding in surgical patients
  - 1. Fatal bleeding, and/or
  - 2. Bleeding that is symptomatic and occurs in a critical area or organ, such as intracranial, intraspinal, intraocular, retroperitoneal, pericardial, in a non-operated joint, or intramuscular with compartment syndrome, assessed in consultation with the surgeon, and/or
  - 3. Extrasurgical site bleeding causing a fall in hemoglobin level of  $20 \text{ g L}^{-1}$  ( $1.24 \text{ mmol L}^{-1}$ ) or more, or leading to transfusion of two or more units of whole blood or red cells, with temporal association within 24–48 h to the bleeding, and/or
  - 4. Surgical site bleeding that requires a second intervention (open arthroscopic, endovascular) or a hemarthrosis of sufficient size as to interfere with rehabilitation by delaying mobilization or delayed wound healing, resulting in prolonged hospitalization or a deep wound infection, and/or
  - 5. Surgical site bleeding that is unexpected and prolonged and/or sufficiently large to cause hemodynamic instability, as assessed by the surgeon. There should be an associated fall in hemoglobin level of at least  $20 \text{ g L}^{-1}$  ( $1.24 \text{ mmol L}^{-1}$ ), or transfusion, indicated by the bleeding, of at least two units of whole blood or red cells, with temporal association within 24 h to the bleeding.

- Mild to moderate bleeding:
  - o All bleeding events that do not meet the International Society of Thrombosis and Haemostasis (ISTH) criteria according to which major bleeding is defined.

Thrombotic event: any arterial or venous thrombosis, including acute myocardial infarction or stroke for arterial thrombosis and deep venous thrombosis or pulmonary embolism for venous thrombosis.

Definition of terms:

- Acute myocardial infarction: Detection of a rise and/or fall of cardiac biomarker values [preferably cardiac troponin (cTn)] with at least one value above the 99th percentile upper reference limit (URL) and with at least one of the following:
  - o Symptoms of ischemia
  - o New or presumed new significant ST-segment–T wave (ST–T) changes or new left bundle branch block (LBBB).
  - o Development of pathological Q waves in the ECG.
  - o Imaging evidence of new loss of viable myocardium or new regional wall motion abnormality.
  - o Identification of an intracoronary thrombus by angiography or autopsy.
- Stroke: an embolic, thrombotic, or haemorrhagic vascular event or stroke with motor, sensory, or cognitive dysfunction (such as hemiplegia, hemiparesis, aphasia, sensory deficit, impaired memory) that persisted for 24 or more hours.
- Deep venous thrombosis: venous thromboembolism is defined as an acute vascular occlusion of an extremity or organ, documented by means of imaging, surgery, or autopsy.
- Pulmonary embolism: the presence of a blood clot in a pulmonary artery with subsequent obstruction of blood supply to the lung parenchyma or if the patient had a ventilation-perfusion scan interpreted as high probability of pulmonary embolism or a positive result on spiral computed tomography, transesophageal echocardiography, pulmonary arteriography, or computed tomography angiography.
- Any objectively determined venous thrombus

***The secondary outcomes are severity of bleeding complication, length of hospital stay, readmissions within 3 months after discharge, quality of life, quality of care (patient satisfaction with antithrombotic therapy), adherence by the patient to the therapy, healthcare costs, adherence by the doctors to the hospital protocol, all-cause mortality and percent time in therapeutic range of vitamin K antagonists.***

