### Secondary Objective(s):

The following secondary objectives when a multidisciplinary antithrombotic team (S-team) is installed in the hospital are:

1. To determine the effect on frequency of bleeding events.
2. To determine the effect on frequency of thrombotic events.
3. To determine the effect on severity of bleeding complications.
4. To determine the effect on length of the hospital stay.
5. To determine the effect on percentage of (re)admissions caused by antithrombotic medication.
6. To determine the effect on quality of life, adherence by the patient to the therapy and quality of care (patient satisfaction with antithrombotic therapy).
7. To determine the effect on adherence to the hospital protocol.
8. To determine the effect on costs.
9. To determine the effect on all-cause mortality.
10. To determine the effect on percent time in therapeutic range of vitamin K antagonists.

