#### 8.1.2 Secondary study parameters/endpoints

- Proportion of patients with  $\geq 1$  bleeding (major bleeding and mild to moderate clinically relevant non-major bleeding) event from time to start with antithrombotic medication (or hospitalization) until 3 months after hospitalization.
- Proportion of patients with  $\geq 1$  thrombotic event from time to start with antithrombotic medication (or hospitalization) until 3 months after hospitalization.
- Severity of bleeding complication
- Length of hospital stay (LOS)
- Percentage of readmissions within 3 months after discharge
- Patient related outcomes (quality of life, adherence of patient to therapy and patient satisfaction with the quality of care of the antithrombotic therapy)
- Adherence to the hospital protocol
- Healthcare costs (labor costs versus costs for bleeding/thrombotic events (including use of antidotes))
- All-cause mortality
- Percent time in therapeutic range of vitamin K antagonists during hospitalization and 3 months after discharge.

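### The stroke definition used for thrombotic events includes haemorrhagic stroke, so a haemorrhagic stroke with a lasting deficit counts as a major bleed and also enters the secondary thrombotic endpoint

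*Protocol*

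**What the plan says.** All the event definitions are in Protocol section 8.3.1.

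- **Thrombotic event.** The umbrella definition reads "Thrombotic event: any arterial or venous thrombosis, including acute myocardial infarction or stroke for arterial thrombosis", followed by the venous forms.
- **Stroke.** In the list of terms under that umbrella, stroke is "an embolic, thrombotic, or haemorrhagic vascular event or stroke with motor, sensory, or cognitive dysfunction", with the condition "that persisted for 24 or more hours".
- **Major bleeding, non-surgical patients.** One criterion is "Symptomatic bleeding in a critical area or organ, such as intracranial".
- **Major bleeding, surgical patients.** The parallel criterion is "Bleeding that is symptomatic and occurs in a critical area or organ, such as intracranial".

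The two kinds of event are also analysed separately. Section 2 lists bleeding frequency as secondary objective 1 and thrombotic frequency as secondary objective 2 ("To determine the effect on frequency of thrombotic events"). Section 8.1.2 makes each a secondary endpoint: the proportion of patients with at least one "bleeding (major bleeding and mild to moderate clinically relevant non-major bleeding) event from time to start with antithrombotic medication", and the proportion with at least one "thrombotic event from time to start with antithrombotic medication (or hospitalization) until 3 months after hospitalization".

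The primary endpoint in section 8.1.1 is the proportion of patients with at least one event of either kind.

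**The concern.** A haemorrhage is not an arterial thrombosis, so the stroke definition contradicts the category it is meant to explain. Someone coding events from the hospital record would apply the itemised definition and record a haemorrhagic stroke with a lasting deficit as a thrombotic event. The same stroke is already a major bleed.

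Bleeding and thrombosis are the two opposing harms of antithrombotic treatment. The protocol does not say why it reports them separately, but a reader will use the two results to see which harm the S-team changed. Under the present wording, a fall in haemorrhagic strokes is partly reported as a fall in thrombosis, and a rise is partly reported as a rise in thrombosis.

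The design adds a second risk. In a before-after comparison, event classification must be the same in both phases. If coders resolve the contradiction differently between hospitals or between phases, the difference enters the comparison directly.

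**Working it through.** **1. Which events meet both definitions**

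| Event | Major bleeding? | Stroke, hence thrombotic? |
|---|---|---|
| Ischaemic stroke, deficit of 24 h or more | No | Yes |
| Symptomatic intracranial bleed without motor, sensory or cognitive deficit, or with one under 24 h | Yes | No |
| Haemorrhagic stroke, deficit of 24 h or more | Yes | Yes |

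Only the third row is counted twice. The bleeding endpoint counts it correctly; the thrombotic endpoint should not contain it.

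**2. The plan's own sample size**

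Section 4.4 gives a composite of 9% against 5.5%, alpha 0.05 and power 0.80. The sidedness is not stated; two-sided reproduces the figure.

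- Mean proportion: (0.09 + 0.055)/2 = 0.0725.
- n = [1.960·√(2·0.0725·0.9275) + 0.8416·√(0.09·0.91 + 0.055·0.945)]² / 0.035² = 860.5, rounded up to 861.
- With continuity correction: n′ = (n/4)·[1 + √(1 + 4/(n·0.035))]² = 917, as stated.

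A patient with a haemorrhagic stroke enters the composite once, through major bleeding, whether or not the stroke is also called thrombotic. Correcting the definition changes neither the observed composite nor the 917.

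**3. Effect on the thrombotic endpoint**

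Inputs from section 4.4: thrombotic rates of 4% before and 3% after (ratio 0.75); 917 per phase; bleeding planned to halve, from 5% to 2.5%.

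Assumptions, because the protocol has no haemorrhagic-stroke rate: a pre-intervention rate *h* of 0.25% to 1.0%; a post-intervention rate *r·h*, with *r* = 0.5 (halved, as planned for bleeding) or *r* = 1 (unchanged); and planned 4% and 3% that contain only true thrombotic events, so that *h* is added to them.

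Ratio as counted = (0.03 + *r·h*) / (0.04 + *h*)

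| *h* | Haemorrhagic strokes before, per 917 | Halved: rates, ratio | Unchanged: rates, ratio |
|---|---|---|---|
| 0.25% | 2.3 | 4.25% vs 3.125%, 0.735 | 4.25% vs 3.25%, 0.765 |
| 0.5% | 4.6 | 4.5% vs 3.25%, 0.722 | 4.5% vs 3.5%, 0.778 |
| 1.0% | 9.2 | 5.0% vs 3.5%, 0.70 | 5.0% vs 4.0%, 0.80 |

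The planned thrombotic counts are 917 × 0.04 = 36.7 and 917 × 0.03 = 27.5. The assumed strokes are 0.25/5 = 5% to 1.0/5 = 20% of the presumed pre-intervention bleeds.

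With *k* = *h*/0.04, the ratio equals (0.75 + *r·k*)/(1 + *k*). The apparent thrombotic effect is exaggerated when *r* is below 0.75 and diluted when it is above. A reversal (ratio above 1) needs *k*(*r* − 1) > 0.25. At the top of the assumed range (*k* = 0.25), haemorrhagic strokes would have to more than double.

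**4. Precision**

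Without continuity correction, power at 917 per phase is about 21% for 4% against 3%, and about 18% to 36% across the cases above. For bleeding (5% against 2.5%) it is about 80% and does not change.

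**The case against.** **The umbrella definition may already exclude these strokes.** It names stroke in the context of arterial thrombosis, and a haemorrhage is not one. On that reading, the later entry only explains the word in general terms. This is the strongest reply, and it shows that the two texts conflict. It does not settle the conflict: the entry names haemorrhagic events outright, and no sentence removes them from the thrombotic count. What stands is that misclassification of every case is not certain, because a coder could follow the umbrella wording instead.

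**The size has no basis in the protocol.** This stands. No haemorrhagic-stroke rate is given. Intensive-care patients are excluded (section 4.3) and consent is sought at discharge (section 11.2), so patients who die in hospital of such a stroke would mostly not be enrolled; that points to smaller counts. The 4% and 3% also derive from annual rates, whereas the endpoint covers the admission plus 3 months. The ratio depends only on *h* relative to the thrombotic rate, so it is unchanged if both scale alike, but the patient counts are not.

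**The endpoint is imprecise anyway.** Also true. The planned difference of about 9 patients has a standard error of √[917·(0.04·0.96 + 0.03·0.97)] = 7.9. Low power is no reason to keep a classification that contradicts its own heading.

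**Stronger readings that a reader might infer, and that the documents do not support:**

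- *Both component endpoints are wrong.* The bleeding endpoint is sound; intracranial bleeding belongs there.
- *Every intracranial bleed counts twice.* Only one with a qualifying deficit of 24 hours or more does.
- *The primary result or the 917 is affected.* The composite counts each patient once. Adding 5% and 4% would hide an overlap only if the 4% already contained haemorrhagic strokes, and section 4.4 does not say so.
- *A fixed share of the planned thrombotic effect is lost.* Any such share needs an assumed net shift in haemorrhagic strokes between phases, which the protocol does not supply.

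**Conclusion.** The point holds in a limited form. As written, section 8.3.1 places a haemorrhagic stroke with a deficit of 24 hours or more in the thrombotic endpoint as well as under major bleeding. The effect is confined to one secondary endpoint and to how clearly it can be told apart from bleeding.

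Under the stated assumptions, the planned thrombotic ratio of 0.75 moves by 0.015 to 0.05 in either direction: down to between 0.735 and 0.70 if haemorrhagic strokes are halved, up to between 0.765 and 0.80 if they are unchanged. This range illustrates the mechanism; it is not an estimate. The contradiction in the definitions does not depend on it.

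It should be corrected because the protocol itself fixes the definition and the correction is nearly free. It does not threaten the primary analysis.

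**What to change.** In section 8.3.1, under thrombotic events:

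1. Delete *haemorrhagic* from the stroke definition, so that it covers embolic or thrombotic (ischaemic) stroke only.
2. State that haemorrhagic stroke, like other symptomatic intracranial bleeding, counts only as major bleeding.
3. Deletion alone leaves two groups unassigned: strokes of undetermined type, and ischaemic strokes with haemorrhagic transformation. State one classification rule for each and apply it identically in both phases and both hospitals.
4. Record stroke type as a code on the case report form.

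The cost is a wording amendment and one data field. Sample size, visits and data sources do not change. If strokes have already been coded under the present wording, only those need rereading, from medical records that the study already uses.
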